## Abstract

**Highlights:**

**What are the main findings?**
Immersive virtual reality can be used as a meditation tool for cancer patients in palliative care.The randomized clinical trial protocol evaluates its effectiveness in pain management and quality of life.

**What are the implications of the main findings?**
Virtual reality meditation may provide a complementary strategy to improve well-being in integrative oncology.The study could generate scientific evidence to support better healthcare decisions in cancer pain management.

**Abstract:**

**Background/Objectives**: Cancer is a disabling, challenging, and growing global disease. Although early diagnosis and adequate treatment of cancer are developing rapidly, a large part of the population remains without access to specialized services and routinely progresses to uncontrolled pain, poorer quality of life, and suffering. Complementary therapies for pain management and the well-being of patients under palliative care are fundamental tools of integrative oncological medicine. This first version of the protocol was created in August 2023 to structure the aim of this study to investigate the effectiveness of the experimental protocol which uses immersive virtual reality as a meditation tool in patients followed at the Pain Therapy and Palliative Care Service of the CECON Foundation. **Methods**: This randomized clinical trial, conducted at the Pain Therapy and Palliative Care Service (STDCP) of the FCECON, explores the use of immersive virtual reality to promote regular meditation practice among cancer patients as an effective means of managing pain and improving quality of life. **Discussion**: The present study has the potential to evaluate the effectiveness of immersive virtual reality as a meditation tool for patients undergoing palliative care, in addition to contributing scientific evidence that supports better decisions in healthcare for the management of cancer pain. Trial registration: Brazilian Registry of Clinical Trials (ReBEC) and ClinicalTrials.gov/NCT06328751/Universal Trial Number (UTN) U1111-1304-3752.

## 1. Introduction

The increase in cancer incidence and mortality remains a global challenge with projections indicating a substantial increase in incidence over the coming decades that will impact health systems already facing ongoing structural limitations [1].

Brazil recorded 627,193 new cancer diagnoses in 2022 and projections indicate that by 2045 the increase will reach approximately 69%, in comparison to 2022 [1], placing cancer among the leading causes of morbidity and mortality in the country, presenting one of the greatest challenges to the public health system [2]. Given these regional and national differences, it is important to define a strategy to allow for equity in access to cancer healthcare [3] since unequal screening coverage and the limited number of specialized cancer centers lead to late diagnoses, reduced survival rates, increased costs, morbidity, and an impact on the quality of life of these patients [2].

Despite significant advances in oncological therapies, pain remains one of the most prevalent and distressing symptoms experienced by patients with cancer [4]. For many patients, pain is the first symptom of the disease, and most experience moderate to intense pain throughout their illness, making it one of the most feared and uncomfortable symptoms reported by cancer patients [5]. A clearer understanding of the mechanisms driving cancer-related pain, along with the integration of effective pain therapies into routine oncological care, is essential to improving both quality of life and survival among patients with cancer [6].

Cancer pain is diverse and multifactorial and results from a set of interactions related to tumor mechanisms such as inflammatory and neuropathic mechanisms and may also be associated with the effects of treatment [7]. Although there is strong evidence that the experience of pain can negatively affect clinical outcomes at all stages of the disease, cancer patients do not always receive adequate pain treatment [6,7].

The World Health Organization’s Analgesic Ladder continues to play a key role in pain treatment and guides pain management according to its intensity [4,8]. However, these guidelines do not address the heterogeneity of mechanisms in patients with different types of cancer, disease stages, and treatment plans. Thus, pain remains a frequent complaint for a significant portion of patients who experience incomplete relief or side effects that limit the dose of medications available in cancer centers and require complementary approaches that address both the physical and psychosocial dimensions of suffering [7,8,9].

Palliative care is an approach to improving the quality of life of patients with life-threatening illnesses that cause enormous family distress [9]. Instead of focusing exclusively on treatments that modify the disease, palliative care prioritizes symptom control, psychosocial support, and the preservation of dignity, meeting the needs of patients and their families throughout the course of the disease [8,9].

Mindfulness is a term that refers to the practice of being intentionally and non-judgmentally attentive in the present moment. Mindfulness meditation is the central component of mindfulness-based interventions that involves the practice of meditation and mindfulness techniques, and it is a skill that can be trained and has several modalities for its development, which may involve breathing techniques, music/sounds, and guided imagery, which encourage a deep state of realignment, attention, and balance of the body and mind [9,10,11].

For individuals experiencing chronic pain, the regular practice of mindfulness has been shown to have consistent and far-reaching positive effects on various aspects of daily life and health [9]. This intervention promotes a reduction in pain perception and contributes to significant improvements in overall functional activity, mood balance, and physical capacity, including walking and performing work activities [10]. Additionally, it positively impacts the quality of interpersonal relationships, sleep patterns, and subjective well-being and life satisfaction [10,11,12].

In individuals living with chronic pain, the practice of mindfulness is associated with reduced pain-related suffering and improvements in functional performance, emotional regulation, sleep quality, and well-being, as there are changes in attention processing and modulation of the neural circuits involved in stress and pain perception [11,12].

Recent studies have examined novel methodologies for mindfulness practices in the context of cancer pain management, with interventions facilitated by digital technologies emerging in a promising trend [13]. By combining guided meditation with immersive audiovisual environments, VR-based interventions may enhance attentional engagement and facilitate transient analgesic effects through mechanisms related to distraction and emotional regulation. Preliminary studies have reported benefits such as increased engagement, promotion of relaxation, and transient pain relief; however, considerable methodological challenges and difficulties related to the usability of these resources persist [14].

Despite the recent surge in research investigating the use of VR-mediated meditation, particularly in cancer patients receiving palliative care, there is an ongoing need for more robust investigations to assess its effectiveness, associated clinical outcomes, and the duration of its effects. Studies suggests that immersive virtual reality may act through multiple neurophysiological mechanisms, particularly those related to conditioning, attention modulation, and therapeutic exposure processes, contributing to the management of cancer pain [15,16].

Thus, the general objective of this study is to investigate the effectiveness of an experimental protocol that uses immersive virtual reality as a meditation tool in patients followed at the Pain Therapy and Palliative Care Service of the CECON Foundation.

## 2. Materials and Methods

### 2.1. Trial Design

The protocol uses an experimental, longitudinal, randomized controlled trial (RCT) approach, conducted at three time points. The experimental design is shown in the flowchart in Figure 1, and the temporal implementation of the experimental protocol is demonstrated in Table 1.

### 2.2. Study Setting

This project was approved on 5 January 2024 by the FCECON Research Ethics Committee under the number CAAE: 76043823.0.0000.0004 and subsequently registered on the following Research Registration Platforms: Brazilian Registry of Clinical Trials (ReBEC) under number 15,398 and ClinicalTrials.gov/NCT06328751/Universal Trial Number (UTN) number U1111-1304 3752.

The research is conducted in the medical office, used by the medical team to care for patients monitored by the Pain Therapy and Palliative Care Service (STDCP) of the Amazonas State Oncology Center Foundation (FCECON). The STDCP has a multidisciplinary team of anesthesiologists specializing in pain therapy, palliative medicine, and acupuncture, nurses, psychologists, physical therapists, chaplains, and nursing technicians. All research processes are carried out in rooms used by the STDCP team and conducted by the team responsible for the protocol. This team includes doctors and medical students trained to explain all phases of the study, its risks, and its benefits; ensure confidentiality before, during, and after the research; and provide compensatory assistance to those who suffer harm from participating in the study.

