### 2.3. Recruitment and Participants

The protocol includes patients between the ages of 18 and 75 who are assisted at the STDCP, with a diagnosis of cancer pain; who can understand Portuguese, have normal vision and hearing, can move their heads, and have sufficient motor control to perform bodily movements; who have a mobile phone with a compatible system; and who agree to participate in the study and sign the informed consent form (ICF).

Indigenous patients were excluded from study due to cultural peculiarities, language, and special legislation. The other exclusion criteria are patients with a history of serious mental illness (DSM-5, Diagnostic and Statistical Manual of Mental Disorders—schizophrenia, schizotypal disorders, delusional disorders, borderline personality disorder, manic phase in bipolar disorder, and dementia); neurological deficits that compromise the degree of cooperation (Glasgow Coma Scale ≥ 14); impaired comprehension and communication skills based on the researcher’s assessment; reports of discomfort when using immersive virtual reality; disease progression that limits regular outpatient mobility; and patients with brain tumors, brain metastases, metastatic lung neoplasm, or a history of seizures.

In order to participate in the study, patients are required to provide informed consent. The consent document includes a comprehensive explanation of the study’s objectives, its potential risks and benefits, and the various stages of the research process. The subjects are then requested to provide their consent and written informed consent is then obtained from all participants.

The protocol stipulates that harm will be defined if any adverse effect occurs after randomization of study participants. The harm will be evaluated systematically at all time points of the study (T1, T2, T3) through the use of structured questionnaires and symptom scales, as well as non-systematically through spontaneous reports from participants. All events will be documented, and serious adverse events will be reported to the ethics committee, as required by Brazilian ethical standards. The ICH Good Clinical Practice (ICH-GCP) definitions will be used to categorize all adverse events.

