In each interview (T1, T2, and T3), all questionnaires are administered before the meditation session (Before Meditation), and only the ESAS is administered immediately after the meditation session (After Meditation) to capture acute changes in symptoms. All assessment instruments are based on questionnaires and assessment scales already validated in the literature and are listed in Table 2.

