### 2.5. Interventions

The study is conducted at three moments (T1, T2, and T3) with all study groups (case group—Group A; active control group—Group B; passive control group—Group C). In T1 of the study, all groups respond to the baseline assessment approach of the study, which consists of a sociodemographic and clinical questionnaire for the three groups. The data is collected at the FCECON office, immediately after these patients have completed their medical appointment at the Pain Therapy and Palliative Care Service at FCECON.

Participants are randomized into three groups: a case group with guided meditation using virtual reality/3D (three-dimensional) video (Group A), an active control group with guided meditation using 2D (two-dimensional) video (Group B), and a passive control group with guided meditation using audio (Group C). All participants are interviewed at three moments: time 1 (T1)—the first day of intervention and collection of instruments; time 2 (T2)—four weeks after T1; time 3 (T3)—eight weeks after T1.

In all groups and at all moments, T1, T2, and T3, patients respond to the sociodemographic and clinical questionnaire and other instruments measuring quality of life, psychological morbidity, pain, and symptoms. After completing the meditation, patients respond to the Edmonton Symptom Assessment Scale.

The randomization sequence and the type of meditation used in each group at the FCECON office are accessible to the research team, but participants are not aware of the other research groups or the type of meditation is used in each group. Data collection takes place separately on different days and at different times, without one participant having access to another’s meditation.

Subsequently to the in-person intervention at the FCECON office, participants from all three groups receive standardized instructions for conducting home meditation. The practice should be conducted using a video previously provided by the research team, accessed on the participants’ own cell phones, without the need for an internet connection, in offline mode.

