#### 2.5.4. Randomization and Blinding

The randomization is performed by the principal investigator using a specific commercial mobile application called Randomizer^®^ for Clinical Trial Lite, which is a secure, validated application that works with encrypted network traffic using TLS (Transport Layer Security), a strong encryption for random distribution among the research groups.

The study is a comparative study; the participants in the case group, active control group, and passive control group are recruited in the same way, receive the same information about meditation, and answer the same questionnaires before and after meditation. However, given the nature of behavioral interventions (virtual reality and 2D video or audio), both participants and research assistants conducting the interventions cannot be blinded to group allocation. The questionnaires used in the study are administered and collected by researchers who are aware of the intervention modality and are responsible for setting up the equipment, training participants, and providing technical support.

To minimize bias, the statistician responsible for the analyses will remain blinded to group allocation, and group labels will be coded during data analysis. We recognize the lack of blinding of the evaluator as a limitation, which will be considered in the interpretation of the results.

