### 2.6. Outcome Measures

The primary outcome of the protocol is the change in pain intensity, measured by the Brief Pain Inventory—Short Form (BPI), from the beginning of the study (T1) to the eight-week follow-up (T3). The item “worst pain in the last 24 h” (numerical scale from 0 to 10) will be used as the indicator of pain intensity, as it has been validated and demonstrated to be clinically important in oncology and palliative care populations.

Secondary outcomes will encompass metrics designed to assess the psychological, functional, and symptomatic domains. Psychological morbidity will be assessed using the Hospital Anxiety and Depression Scale (HADS), including total and subscale scores. Quality of life will be evaluated using the McGill Quality of Life Questionnaire.

In addition to longitudinal assessments at T1 (baseline), T2 (four weeks), and T3 (eight weeks), the immediate pre- and post-intervention effects will be explored using the Edmonton Symptom Assessment Scale (ESAS). The ESAS will be administered prior to and following each in-person guided meditation session to assess acute changes in symptoms. Pain intensity, severity, and interference will be measured using the respective subscales of the BPI. The extent to which participants adhere to the intervention will be determined by calculating the percentage of prescribed meditation sessions completed during the follow-up period.

The subsequent Table 3 offers a synopsis of all outcome measures, variables, analysis metrics, aggregation methods, and assessment time points.

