While the existing literature demonstrates the benefits of VR in chronic pain contexts, with significant reductions in pain intensity, psychological distress, and functional disability, the present protocol seeks to expand this discussion of evidence to a scenario that has been little explored: cancer pain in palliative care [25,26].

Another aspect to consider is the emotional and psychological state of patients. Evidence indicates that emotional distress acts as a modulator of pain perception and response to non-pharmacological interventions [9]. Meditation can promote significant improvement in quality of life, as demonstrated even in populations with high psychological morbidity [10,23]. However, for these benefits to remain consolidated, continuous practice is essential, which makes adherence a critical variable.

Moreover, the extant literature acknowledges that in randomized trials, equivalence of duration between groups is not a methodological requirement. Consequently, these groups are capable of participating in sessions of varying durations, as the duration of interventions is no longer regarded as a limitation, in contrast to conventional mindfulness programs [26]. Studies have demonstrated that there are no substantial discrepancies between the short-term and long-term consequences of interventions that utilize brief meditation techniques to enhance well-being [27].

This scenario should be carefully considered in the final analysis of the results, since differences observed between modalities may reflect both the intrinsic effectiveness of each meditation format and the ability of each patient to maintain the proposed practice. Future research should explore strategies to optimize adherence, such as active remote support, hybrid sessions (in person and at home), or personalized adaptations to the patient’s clinical profile.

It is important to note that this protocol is vulnerable to certain limitations, particularly in cases involving patients receiving palliative care in the terminal phase of the disease. These limitations may include loss to follow-up due to death, the emergence of uncontrollable pain from disease progression, and the combination of pharmacological therapies such as chemotherapy, which can cause side effects and symptoms that are complex to manage.

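### Outcome collection is tied to clinic visits with no remote fallback, so patients who worsen are the most likely to lack the T3 worst-pain score

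*Protocol article*

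**What the plan says.** All quotations are from the protocol article.

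- **Place.** Section 2.2: "All research processes are carried out in rooms used by the STDCP team and conducted by the team responsible for the protocol". Section 2.5, in the paragraph on T1: "The data is collected at the FCECON office, immediately after these patients have completed their medical appointment".
- **Occasion.** Section 2.4: "In each interview (T1, T2, and T3), all questionnaires are administered before the meditation session (Before Meditation"). Table 2 repeats this for T1, T2 and T3.
- **Mode.** Section 2.5.4: "The questionnaires used in the study are administered and collected by researchers who are aware of the intervention modality". The same staff set up the equipment.
- **Primary outcome.** Section 2.6 defines it as the change in pain intensity from T1 to T3 at eight weeks: "The item “worst pain in the last 24 h” (numerical scale from 0 to 10) will be used as the indicator of pain intensity".
- **Expected loss.** Section 3.1 calls attrition in palliative oncology high and allows 12% for loss to follow-up. Section 4, on limitations: "These limitations may include loss to follow-up due to death, the emergence of uncontrollable pain from disease progression".
- **Telephone.** Section 2.3 restricts entry to patients "who have a mobile phone with a compatible system". Section 2.5 sends meditation reminders to those phones twice a week for eight weeks.

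The article describes no telephone, home or other remote assessment of any outcome.

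**The concern.** Attending a clinic at week 8 requires a patient to be well enough to travel. In this population a common reason for not being well enough is the quantity that the trial measures. If the score can be given only at a visit, the chance that it is missing rises with its own unobserved value. Analysis cannot repair that without untestable assumptions, so the remedy lies in how the score is collected.

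Two results are at stake. The first is the change from baseline in each arm, which Table 3 lists for the primary outcome and which would lean towards patients well enough to attend. The second is the comparison between arms, which is distorted if the arms lose different numbers of patients or patients of different severity. In addition, repeated-measures ANOVA (section 3.2) in its standard form drops a patient with any missing time point, so a missed T2 or T3 can also cost that patient's other values.

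The clinic visit is not needed to obtain this score. It is one number, it is asked before the session, and every participant has a phone.

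**Working it through.** **1. The plan's own figures.** There are 129 participants, 43 per arm, with 12% loss expected (section 3.1). Patients with a T3 value: 43 × 0.88 = 37.8 per arm, and 129 × 0.88 = 113.5 in all, against the 117 wanted. If calls recovered half of the losses (assumption), 129 × 0.94 = 121.3 would have a value. At three quarters (assumption), 129 × 0.97 = 125.1.

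**2. Closed form for the T3 mean.** Let m be the share missing in an arm and D the amount by which missing patients score worse than observed ones. The true mean is (1 − m) × observed + m × (observed + D), so

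observed mean − true mean = −m × D.

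The document does not give D. For D = 1 to 4 points and m = 0.12, each arm's mean T3 pain looks 0.12 to 0.48 points too low. The between-arm bias depends on the difference in m × D:

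- equal m and equal D: bias 0;
- 6% v 18% loss (assumption) and D = 3: (0.18 − 0.06) × 3 = 0.36 points, or 0.18 if half of the losses are recovered.

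**3. Simulation of the change score.** Patients who are worse at T3 also tend to have been worse at T1, so the bias in the change is smaller than in the T3 mean. The document gives no SD, T1–T3 correlation or loss by arm, so every input here is an assumption:

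- 0–10 scores, rounded and bounded;
- T1 mean 6, control T3 mean 5, true difference of about 1 point in favour of the other arm;
- SD 2.0 to 2.5 and correlation 0.3 to 0.7;
- 8% loss when T3 pain is below 7;
- 30%, 50% or 70% non-attendance when T3 pain is 7 or more;
- 400,000 patients per arm, two arms for simplicity.

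| Non-attendance at T3 pain ≥ 7 | Loss, control v other arm | Control improvement overstated by | Arm difference shrinks by |
|---|---|---|---|
| 30% | about 13–14% v 10–11% | about 0.05–0.15 | about 0.02–0.05 |
| 50% | about 17–20% v 12–15% | about 0.1–0.3 | about 0.04–0.10 |
| 70% | about 22–25% v 15–18% | about 0.16–0.49 | about 0.07–0.17 |

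The true control improvement is just under 1 point. The 30% row is nearest the planned 12% loss. A higher T1–T3 correlation gives less bias. Loss differs by arm here only because the better arm has fewer patients at 7 or above, so the bias pulls the difference towards zero.

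**The case against.** **The text is less categorical than the problem sounds.** A reader might infer that the patients who worsen are exactly those with no T3 value. The documents do not support that. The Discussion lists such loss only as something the limitations may include. Section 2.2 is a statement of setting and cannot be literal, because home meditation and reminders happen elsewhere. The sentence on office collection in section 2.5 is in the T1 paragraph. This stands, so the claim is about who is most likely to be missing. It remains true that every outcome questionnaire is placed at an in-person interview and none elsewhere.

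**Handling of missed visits belongs in a full protocol.** An article commonly omits visit windows and contact logs, and their absence is no finding. The point here is the collection method that the article does state, which as written leaves no room for a value from a patient who cannot attend.

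**The effect on the randomized comparison may be small.** This stands. With equal loss and equal severity there is no between-arm bias, and near the planned loss the illustration gives only hundredths of a point. A reader might infer a spurious benefit for virtual reality. The document gives no basis for that, and in the illustration the difference is attenuated. Neither the size nor the direction can be derived from the article.

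**Not all of the loss is avoidable.** This also stands. Deaths and patients too ill to answer stay missing, and nothing shows how many non-attenders would take a call.

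**The risk is partly addressed.** Section 2.3 excludes progression that limits outpatient mobility, sample size allows for loss, and the limitation is disclosed. At entry the exclusion removes those least able to attend. It does not help those who progress during the eight weeks, and the article does not say whether it also applies after randomization. If it does, it would add to the loss.

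**Conclusion.** The point holds as a cheap improvement to a stated collection method. Followed as written, the plan makes the primary score most likely to be missing where pain is worst, and within-arm improvement would tend to be overstated. Between-arm bias needs loss, or the severity of those lost, to differ by arm.

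Under the assumptions in the working, the effect on the arm comparison is modest: a few hundredths of a point near the planned 12% loss, and up to about 0.17 of a true difference of about 1 point when 70% of those with severe pain do not attend. The within-arm overstatement is larger, from about 0.05 to about 0.49 points over the same range. These figures show scale and are not forecasts for this trial. The conclusion about who is likely to be missing rests on the article's own text and does not depend on them.

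**What to change.** In sections 2.4 and 2.5, state that a participant who cannot attend T2 or T3 is telephoned by the existing team within a fixed window around the due date, identically in all arms, to obtain at least the BPI worst-pain item. Record the mode of collection (office or telephone) and the reason for non-attendance. Amend the sentence on location in section 2.2 to match.

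The cost is protocol wording and a few short calls. The downside is a possible difference between office and telephone answers, which the recorded mode helps to examine. Calls cannot recover deaths, patients too ill to answer, or the post-session ESAS, so the limitation in the Discussion should stay.
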